### Process evaluation

A process evaluation will be undertaken ‘to explain discrepancies between expected and observed outcomes, to understand how context influences outcomes, and to provide insights to aid implementation’ [43]. We will use a modified version of Linnan and Steckler’s framework for process evaluation [44]. The context for intervention implementation will be explored using qualitative interviews, schedules for which will be developed by a multidisciplinary team including potential participants and will investigate whether the intervention, when scaled up, is appropriate for and acceptable to mental health services (i.e. facilitators) and service users. We will explore other aspects (e.g. reach, dose delivered and received) quantitatively.

The methods of recruitment will also be explored both qualitatively and quantitatively. We will not produce a composite score for implementation as proposed by Linnan and Steckler, as we do not believe such a score would have validity or utility for our intended audience.

### Qualitative component of STEPWISE trial

#### Participant interviews

Approximately 20–24 participants will be purposively sampled, from those consenting to be contacted about the qualitative interview, to recruit different genders and ages.

All interviews will be via telephone or face-to-face and last about 1 h depending on the participant’s response and wishes. Interviews will not be conducted until after the 3-month follow-up visit. The qualitative research will also inform the quantitative aspects of the process evaluation.

A semistructured interview topic guide, will contain general open questions exploring the experience and acceptability of the intervention to participants. It will also include questions intended to elicit themes outlined in the existing published literature such as the barriers to, and facilitators of, the use of lifestyle interventions in people with schizophrenia [45–47].

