**Methods:**

Design: a randomised controlled trial of a group-based structured education programme.

Setting: 10 UK community mental health trusts.

Participants: 396 adults with schizophrenia, schizoaffective, or first-episode psychosis who are prescribed antipsychotic medication will be recruited. Participants will be overweight, obese or be concerned about their weight.

Intervention: participants will be randomised to either the intervention or treatment as usual (TAU). The intervention arm will receive TAU plus four 2.5-h weekly sessions of theory-based lifestyle structured group education, with maintenance contact every 2 weeks and ‘booster’ sessions every 3 months. All participants will receive standardised written information about healthy eating, physical activity, alcohol and smoking.

Outcomes: the primary outcome is weight (kg) change at 1 year post randomisation. Secondary outcomes, which will be assessed at 3 and 12 months, include: the proportion of participants who maintained or reduced their weight; waist circumference; body mass index; objectively measured physical activity (wrist accelerometer); self-reported diet; blood pressure; fasting plasma glucose, lipid profile and HbA_1c_ (baseline and 1 year only); health-related quality of life (EQ-5D-5L and RAND SF-36); (adapted) brief illness perception questionnaire; the Brief Psychiatric Rating Scale; the Client Service Receipt Inventory; medication use; smoking status; adverse events; depression symptoms (Patient Health Questionnaire-9); use of weight-loss programmes; and session feedback (intervention only). Outcome assessors will be blind to trial group allocation.

Qualitative interviews with a subsample of facilitators and invention-arm participants will provide data on intervention feasibility and acceptability. Assessment of intervention fidelity will also be performed.

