## Aims and objectives

The aim of the STEPWISE trial is to evaluate the extent to which a structured lifestyle education programme, when delivered to adults with schizophrenia, including those with schizoaffective disorder or first-episode psychosis, in a community mental health setting, can support weight loss at 1 year.

Having adapted the DESMOND ‘Lets Prevent’ intervention for people with schizophrenia, schizoaffective disorder or first-episode psychosis and their health care professionals [24], the specific objectives of the trial are:To undertake a multicentre RCT to test the hypothesis that a structured self-management lifestyle education programme can lead to a significant increase in physical activity and improved diet leading to clinically relevant weight loss after 1 yearTo ensure fidelity of the intervention when scaled up, through a robust assessment of its deliveryThrough qualitative research, to assess whether the intervention, when scaled up, is appropriate for and acceptable to mental health services and people with schizophrenia, schizoaffective disorder or first-episode psychosisTo undertake an economic evaluation of the interventionTo develop a quality assurance framework for facilitators delivering the intervention

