#### STEPWISE education programme

The intervention lasts for approximately 12 months. Participants allocated to the intervention will receive a foundation course of four weekly 2.5-h (including breaks) group sessions delivered by two trained facilitators. The group sessions will involve approximately six to eight participants, although this may vary due to recruitment and attrition. The foundation course will be followed by 1:1 support contact lasting about 10 min, approximately every 2 weeks for the remainder of the intervention period, from a facilitator in order to support behaviour change. Ideally, support contact will be personalised and carried out face-to-face or by telephone. Participants will be invited to attend group-based booster education sessions at 4, 7 and 10 months post randomisation. Group attendance and receipt of support contact will be recorded.

Intervention sessions include: individual personal stories; taking control of weight; healthier food and drink choices; the relationship between weight and medication; and the relationship between calories and portions and physical activity (see Additional file 1). The intervention has a written curriculum to ensure consistency and resources that are in line with meeting its person-centred philosophy. Participants will not be ‘taught’ in a formal way, but rather supported to discover and work out knowledge for themselves, and to allow this to inform their goals and plans.

Participants attending education sessions will be invited by facilitators to complete a ‘Session Feedback’ form at the end of each session. The aim is to capture a self-report of empowerment and health belief during the course; the facilitators will not read the forms. Participants are not encouraged to bring someone with them to the intervention sessions; however, if they do, this will be documented.

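### Attendance is not among the stated sampling criteria for the participant interviews, so the views of people who never started or stopped early are not secured and acceptability may be overstated

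*Protocol article*

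**What the plan says.** One of the specific objectives, under Aims and objectives, is "to assess whether the intervention, when scaled up, is appropriate for and acceptable to mental health services and people with schizophrenia". The Abstract assigns this to interviews: "Qualitative interviews with a subsample of facilitators and invention-arm participants will provide data on intervention feasibility and acceptability". The Process evaluation section gives the wider purpose, which includes "to explain discrepancies between expected and observed outcomes".

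The Participant interviews section sets the number at roughly 20–24 and the selection rule: "participants will be purposively sampled, from those consenting to be contacted about the qualitative interview, to recruit different genders and ages". It also sets an earliest date: "Interviews will not be conducted until after the 3-month follow-up visit". The topic guide covers experience and acceptability, and also "barriers to, and facilitators of, the use of lifestyle interventions in people with schizophrenia".

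Two other statements bear on the point. The section on the STEPWISE education programme says "Group attendance and receipt of support contact will be recorded". The Process evaluation section says "We will explore other aspects (e.g. reach, dose delivered and received) quantitatively".

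**The concern.** The programme consists of four weekly group sessions, boosters at 4, 7 and 10 months, and support contact about every two weeks. In such a programme, never starting or stopping early is the plainest behavioural sign that it did not suit someone. Purposive sampling is meant to make sure that the informative kinds of case are present. Gender and age do not do that here. If the rule is followed as written, every interview can be with a regular attender and the rule is still met.

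Two things are at stake. The acceptability conclusion could rest mainly on those who found the programme acceptable enough to keep attending. And if the trial shows little effect because people stopped coming, the process evaluation could count the stopping but might hold few first-hand accounts of why.

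**Working it through.** **What the stated frame secures.** No published figure needs reproducing, so the first step is to see which planned sources could supply the reasons of someone who never started or stopped early.

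- *Participant interviews.* The stated conditions are agreement to be contacted, and a spread of gender and age. Such a person may be included, but nothing ensures it.
- *Session feedback forms.* These are completed by people at a session and capture empowerment and health belief. Non-starters complete none, and early stoppers complete none after they stop.
- *Reach and dose received.* These are explored quantitatively. They show how many stopped, not why.
- *Facilitator interviews (about 20).* These give health professionals' views on bringing the programme into practice, not participants' own reasons.
- *Attendance records.* These are collected, so an attendance criterion could be applied without new data.

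**How far the sample could tilt.** The article gives no rate of non-attendance. The 20% in the Sample size section is dropout that reduces the number analysed, not failure to attend the programme, so it cannot stand in for one. Both inputs below are assumptions:

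- *p*, the share of the intervention arm who never start or stop early: 10–40%.
- *r*, their chance of being interviewed relative to attenders: 1, 0.5 or 0.25.

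The share of such people among interviewees is q = p·r / (p·r + 1 − p), and the expected number among m interviews is m·q. For p = 0.20 and r = 0.5, q = 0.10 / (0.10 + 0.80) = 0.111, and 20 × 0.111 = 2.2.

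Expected number among 20 interviews (among 24 in brackets):

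| p | r = 1 | r = 0.5 | r = 0.25 |
|---|---|---|---|
| 10% | 2.0 (2.4) | 1.1 (1.3) | 0.5 (0.6) |
| 20% | 4.0 (4.8) | 2.2 (2.7) | 1.2 (1.4) |
| 30% | 6.0 (7.2) | 3.5 (4.2) | 1.9 (2.3) |
| 40% | 8.0 (9.6) | 5.0 (6.0) | 2.9 (3.4) |

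If selection takes no account of attendance, the number is roughly binomial(m, q). With p = 20% and m = 20, the probability of fewer than three such interviewees is 0.21 for r = 1, 0.61 for r = 0.5 and 0.89 for r = 0.25.

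**Reading the results.** With r = 1 there is no systematic under-representation, yet at p = 20% chance alone still leaves about a one-in-five risk of fewer than three. Any systematic tilt comes entirely from r below 1, which is plausible but which the article neither states nor allows one to estimate.

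**The case against.** The strongest reply is that this is a journal article condensing a full protocol that is not shown. A detailed qualitative sampling matrix may sit there, and the article does not say that gender and age are the only criteria. This stands as a caveat: if the full protocol already samples on attendance, only the wording needs to change. It does not dispose of the point, because the article does state its criteria, and the two it names do not serve the objective they are meant to serve.

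Three stronger readings are tempting and should be resisted.

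- *That non-attenders are excluded or certain to be under-represented.* Nobody is ruled out for not attending. The article does not say when consent to contact is taken; if it was taken before allocation, it could not depend on attendance.
- *That the sample is selected on attendance.* Attendance plays no stated part in selection, and that is the weakness. Limiting interviews to people who agree to contact is unavoidable and would remain after any change.
- *That interviewing after 3 months screens out those who stopped.* The rule sets an earliest date and does not require that the visit was attended. Four weekly sessions would normally be over by then, so the delay helps to identify non-starters and early stoppers.

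It is also fair to say that the topic guide asks about barriers, and that measured reach and dose would be read beside the interviews, so poor uptake would not be hidden. That softens the concern. Barriers questions, however, are answered only by those interviewed, and uptake figures carry no reasons.

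**Conclusion.** The point holds as a weakness in the stated sampling frame. Attendance is not a named criterion, so the inclusion of people who never started or stopped early is left to chance and to their willingness to take part, and acceptability may be overstated. The documents do not show that it will be.

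Over the assumed ranges, the expected number of such people among 20 interviews runs from 2–8 (equally likely to be interviewed) to about 0.5–3 (a quarter as likely). Those limits rest wholly on the assumed non-attendance share and relative chance of interview; they show sensitivity and are not estimates. The case for an attendance criterion does not need a proven bias, since securing such cases is the reason to sample purposively. The consequence is confined to the acceptability objective and the process evaluation. The primary analysis of weight change is not affected.

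**What to change.** Within the same 20–24 interviews, add recorded attendance as a purposive criterion alongside gender and age, so that non-starters and early stoppers are deliberately included. The exact number is best left to the qualitative team. Report interviewees' attendance with the acceptability findings, so that readers can see whose views they rest on.

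An optional clarification is to state that a missed 3-month visit does not rule out an interview.

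The cost is a sentence or so in the sampling plan, using data already collected and adding no interviews. The downside is that low attenders are harder to reach and slightly fewer full attenders are heard. The Trial status section says that recruitment has finished and follow-up is under way. If some interviews are already done, the criterion can guide those that remain, and interviewees' attendance can be reported for all.

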#### Facilitators interviews

The process evaluation will explore health care professionals’ views on the experience of incorporating the lifestyle intervention into practice through individual semistructured interviews with approximately 20 facilitators.

May’s ‘Normalisation Process Theory’ (NPT) will be used as a theoretical framework to understand better the conditions necessary to support the introduction, embedding and integration of protocolised lifestyle interventions as routine elements of care [48]. While NPT emphasises the influence of social systems on behaviour, the study will also utilise relevant domains from the Theoretical Domains Framework (TDF) [49, 50] which emphasises individual influences on behaviour. We will also collect facilitator characteristics (e.g. level of education). The process evaluation will inform the interpretation of the trial results and subsequent policy-making, in line with the MRC’s Complex Intervention Framework [43].

All semistructured interviews will be audio-taped and fully transcribed using the National Centre for Social Research ‘Framework’ approach [51].

#### Facilitator training and assessment of intervention fidelity

A fidelity assessment will be undertaken to investigate whether the intervention can be delivered faithfully when scaled up. As the facilitators’ delivery of the intervention is key, an assessment of facilitator performance in each of the participating centres will be conducted during the RCT.

The facilitator training programme and intervention fidelity checks will be undertaken through the DESMOND collaborative and based on the standardised and established criteria currently used to provide quality assurance in the DESMOND National Programme.

During the trial, the delivery of individual facilitators at each centre will be assessed against criteria derived directly from the STEPWISE programme. This will enable the study team to identify if there is any deviation from the delivery taught in training, and will also provide evidence for establishing a benchmark for delivery and facilitator competencies when the intervention is scaled up. All training and assessment procedures will be supportive and transparent.

Although it is not possible to identify the final suite of intervention fidelity tools, these are likely to include assessment of content delivery; assessment of facilitator behaviour against a set of criteria derived from the STEPWISE programme itself; and assessment of facilitator talk time, using the DESMOND Observational Tool (DOT). The latter assessment involves an independent assessor scoring activity in the session (e.g. who is speaking; miscellaneous activity) through use of a 10-s audio prompt (audible only to the assessor). It has been shown that the amount of time facilitators or participants spend speaking is predictive of the changes observed in the participants’ illness perceptions: less facilitator talk leads to a greater change in participants’ beliefs about their condition [36] and is a precursor to behaviour change. Intervention fidelity assessments will be used to inform the outcomes of the trial.

### Trial supervision

Sheffield Health and Social Care NHS Foundation Trust will act as the sponsor for the trial and, therefore, will have overall responsibility for the trial along with the chief investigator. Trial management will be provided by the Sheffield Clinical Trials Research Unit (CTRU), which adheres to its Standard Operating Procedures. The study will use the CTRU’s in-house, access-controlled, data management system for the capture and storage of participant data. Level and frequency of monitoring has been agreed with the sponsor. Three committees will govern the conduct of this study: the Trial Steering Committee (TSC); the Data Monitoring and Ethics Committee (DMEC); and the Trial Management Group (TMG). The TMG will oversee the day-to-day management of the trial. The DMEC is the only group with access to the unblinded outcome date while the trial is underway.

## Discussion

Several previous RCTs [16, 17] and long-term observational studies [35] have shown that lifestyle interventions are effective among people with schizophrenia. However, the current RCT data are limited because of the small numbers of participants involved and their short duration. In addition, few studies have included people with a first episode of psychosis and yet weight gain occurs commonly and rapidly in this group of individuals after treatment initiation. This trial will address these limitations by recruiting a large number of participants who will be followed for a year. We have also specifically included people with first-episode psychosis, where the aim of the intervention may be the prevention of weight gain rather than weight loss.

The importance of managing obesity and overweight in people with schizophrenia is recognised in a number of national and international guidelines. These advocate regular assessment of weight and the implementation of lifestyle modification to address weight gain. Despite the NICE guidance that recommends provision of a combined healthy eating and physical activity programme by mental health care providers, there is uncertainty about how to implement this, reflected by the large variation in the provision of care between different NHS trusts. This trial is being undertaken in 10 mental health trusts from differing geographical areas in England, serving different populations, to maximise generalisability of the findings. If this trial shows the STEPWISE intervention to be effective, the diversity of centres in the study should aid the implementation of the intervention more widely across the NHS.

The intervention is based on the existing Let’s Prevent programme of the DESMOND collaborative. The DESMOND programme is approved by the NICE for people with, or at risk of, type 2 diabetes. It has a well-established training and evaluation process, which could be extrapolated to mental health care professionals wishing to implement STEPWISE.

Although lifestyle programmes have been introduced in some mental health settings, no research has been performed to determine the acceptability of these programmes. People with severe mental illness have similar levels of interest in their cardiovascular health as the general population but are not always able to prioritise their physical health [52]. It is important to assess the acceptability of lifestyle programmes for patients and mental health care professionals. This trial will provide information about this issue.

Treating obesity with either lifestyle or pharmacological interventions is cost-effective in the general population but it is important to evaluate whether this is true for people with schizophrenia. The DESMOND programme has been shown to be cost-effective; using 2010 real-world costs of the intervention, the lifetime incremental cost was £82 and mean incremental cost per QALY was £2113 [53].

By 11 September 2015 the trial had met (and in some instances substantially exceeded) feasibility criteria included in the internal pilot which included the number of recruiting sites, the number of recruited participants, the delivery of the first STEPWISE intervention and rates of retention at 3 months.

### Protocol changes

The trial is largely being conducted as it was originally envisaged. Prior to starting the trial, the method of calculating the primary outcome (weight) was altered from absolute weight to change in weight (kg) following advice received from the first TSC meeting. A small number of other modifications have been made, some of which were a result of the Intervention Development Study whilst others relate to the group-based intervention (e.g. sites were encouraged to recruit in waves not too far ahead of a scheduled course).

In conclusion, the STEPWISE trial will provide evidence for the clinical and cost-effectiveness of a group-based structured education programme designed to help people with schizophrenia, schizoaffective disorder or first-episode psychosis to lose weight or attenuate weight gain. If the intervention is successful, the design of the intervention and trial will allow a rapid dissemination within the NHS.

### Trial status

Participant recruitment finished on 31 March 2016 (*n* = 414 recruited) and the trial is in follow-up.

## Abbreviations

CEACs: Cost-effectiveness acceptability curves
CMHT: Community mental health team
CONSORT: Consolidated Standards of Reporting Trials
DESMOND: Diabetes Education and Self-management for Ongoing and Newly Diagnosed
DOT: DESMOND Observational Tool
EQ-5D-5L: EuroQol five dimensions, five levels questionnaire
GEE: Generalised estimating equation model
ICD-10: *International Classification of Diseases (version 10)*
ICERs: Incremental cost-effectiveness ratios
MRC: Medical Research Council
NPT: Normalisation Process Theory
OPCRIT: OPerational CRITeria checklist for psychotic illness and affective illness
QALY: Quality-adjusted life year
RCT: Randomised controlled trial
SF-36: 36-Item Short Form Survey (RAND Health)
STEPWISE: STructured lifestyle Education for People WIth SchizophrEnia
